Individuals with substance use disorders typically show an attentional bias to substance-related cues. The attention bias is thought to develop as a consequence of a classical conditioning process. One general model of addiction (Franken et al, 2003) suggests that perception of substance-related stimuli lead to increased dopamine level in corticostriatal circuits that draw the subject’s attention towards the perceived substance. The increase in attention promotes craving that further increase the attentional bias. The combination of increased attentional bias and craving increase the probability of substance use and relapse. An Attentional bias towards substance related cues also lead to increase in substance related cognitions (obsessive thoughts about the substance) and to decrease in the ability to execute coping or control strategies that are based on other cues. These two processes work together to increase and maintain an attentional bias towards substance related cues. Most models of addiction (Field et al, 2014) suggest that a) attentional bias for substance-related cues is a characteristic of substance use disorders, b) the bias is associated with the strength of craving at that moment in time and c) strong attentional bias increase the risk of relapse to substance use in those attempting to remain abstinent or to reduce their substance use.

A common paradigm to study attentional bias in substance use disorders is to present subjects with neutral images (desks, pens, etc.) and substance-related images and measure differences between behaviors (reaction time, eye movements) and/or neural activity (EEG, fMRI) when these two classes of stimuli are viewed. We will use the free viewing paradigm and 16 slides to study attentional bias to smoking related cues. Each slide will include an image of smoking related cues (cigarettes, people smoking), an image of a neutral object and two high valence images. The positions (top-left, top-right, bottom-left and bottom-right) of the three different images will be randomly distributed between the slides.

*Attentional bias to negative emotional cues*

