Sensation seeking behavior is common in people with substance use disorders and is correlated with vulnerability to substance addiction (Wingo et al, 2016). Sensation seeking behavior is believed to have a biological basis that is expressed as a need for physiological arousal, novel experience, and a willingness to take social, physical, and financial risks to obtain such arousal (Zuckerman et al, 1979, Bardo et al, 1996). The severity of mal-adaptive patterns of novelty seeking behavior are correlated with substance abuse (Wingo et al, 2016, Stacy et al, 1993) and with vulnerability to the initiation of substance self-administration and compulsive substance use (Belin et al, 2012). Moreover, some studies suggest that sensation seeking behavior can predict treatment outcome and relapse (Ismael et al, 2014, Kahler et al, 2009). We hypothesize that sensation seeking behaviour, as measured by attentional bias to high -arousal/high-risk cues, will be correlated with the probability of remaining abstinent over the long term. To test this hypothesis we will use the free viewing paradigm and 16 slides. Each slide will include an image with high-arousal/high risk scenario, image of a neutral object and two images with positive high valence scenarios. The positions (top-left, top-right, bottom-left and bottom-right) of the three different images will be randomly distributed between the slides. We will study the correlation between attentional bias to high arousal/high risk cues and the standard assessment of sensation seeking behavior (Zuckerman et al., 1978), and also the extent to which tDCS affect novelty seeking behaviour.

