For the eye-tracking data, gaze position data are processed by VAST into sequences of fixations and saccades and summary statistics of visual scanning parameters are computed. The VAST parameters include: the number of fixations, the average fixation duration, the average saccadic amplitude and the number of transitions for each image type. These parameters are sensitive measures of attentional bias for different visual cues. The outcome measures of this paradigm will be analyzed using a mixed-model analysis of variance (ANOVA). The within-groups factors are the image types (smoking, neutral, high valence) and session (sessions 1, 2, 3,4 and 5) and the between-groups factor is group (active tDCS and sham tDCS). Pearson’s product–moment correlations will be conducted between parameters of attentional bias and subjective craving scores. Through analysis, we will investigate and compare the treatment effects of varenicline and active tDCS on attentional bias in different sessions. We will also examine the relationship between changes in attentional bias and craving.

By means of a mixed design repeated-measures ANOVA, the VAST parameters will be compared within-subjects at 5 sessions to investigate the effects of varenicline treatment. The parameters will also be compared between the two groups of subjects to examine the treatment effects of active tDCS. We will also compare the VSB parameters of those who quit smoking in the last 4 weeks of treatment and those who were unable to remain abstinent to find out the possible indicators of treatment outcome. Pearson correlation method will be used to explore the relationships between: a) subjective craving and VSB parameters, b) sensation seeking behavior as measured by the sensation seeking scale measures and VSB parameters. Also we will use recurrent neural networks (Chung et al, 2018) to analyze differences between fixation sequences of patients that were treated with tDCS and patients that were not, and between patients that quit smoking and those that were not. Using Cox regression of survival analysis, we will also investigate the correlation between the length of abstinence (time to relapse) and VSB parameters associated with smoking cues, negative emotional cues and high-arousal/high-risk cues.

All data analysis will be conducted using SPSS, SPM or R as appropriate.

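### Fixation and transition counts per image type build a smoking-versus-high-valence difference into the eye-tracking ANOVA, and without normalisation they also move with total fixations

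*Protocol*

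**What the plan says.** The eye-tracking part of Data Analysis (Protocol) names four parameters: "the number of fixations, the average fixation duration, the average saccadic amplitude and the number of transitions for each image type". It adds: "These parameters are sensitive measures of attentional bias for different visual cues". The model is a mixed ANOVA: "The within-groups factors are the image types (smoking, neutral, high valence) and session", with five sessions, and arm as the between-groups factor. The same section also compares the parameters within subjects over the five sessions to study the effect of varenicline.

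The slide layouts are under Eye-Tracking Method. The smoking test uses "16 slides to study attentional bias to smoking related cues"; besides the smoking image, each slide holds "an image of a neutral object and two high valence images". The high-arousal/high-risk slides follow the same pattern: "image of a neutral object and two images with positive high valence scenarios". The emotional-face slides show four different expressions, one image each. Every slide has four images and is shown for 10.5 seconds. Neither place says that counts are divided by the number of images of a type or by total fixations.

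**The concern.** Two of the four parameters are counts per image type, and the types do not have equal numbers of images on the smoking and high-risk slides. High valence has two chances to be looked at for each one of smoking or neutral. The image-type term for these counts therefore mixes preference with layout.

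A count also scales with how many fixations a person makes. If that total changes between sessions, differences between types change too, even when attention is divided exactly as before. Hypothesis 3 predicts lower bias than at baseline under varenicline. Both arms take varenicline, so no control arm removes a common drift from that comparison. Attentional bias is among the key secondary outcomes. The primary abstinence outcome is not touched.

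**Working it through.** The protocol gives no figure for these scores, so there is none to reproduce.

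**Inputs from the protocol:** four images per slide; 1 smoking : 1 neutral : 2 high valence; 16 smoking slides; five sessions; 25 participants per arm.

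**Assumption:** total fixations per slide, N. The base case is 30, with a range of 20 to 35.

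**1. No preference, fixations.** Each image draws N/4, so smoking = 0.25N, neutral = 0.25N and high valence = 0.50N. Smoking minus high valence = 0.25N - 0.50N = -0.25N. Smoking minus neutral = 0.

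| N | smoking | neutral | high valence | smoking - high valence |
|---|---|---|---|---|
| 20 | 5 | 5 | 10 | -5 |
| 24 | 6 | 6 | 12 | -6 |
| 30 | 7.5 | 7.5 | 15 | -7.5 |
| 35 | 8.75 | 8.75 | 17.5 | -8.75 |

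**2. No preference, transitions.** Suppose each move goes to any of the other three images with probability 1/3. Moves into smoking: 3 × 1/4 × 1/3 = 1/4; neutral is the same. Moves into high valence from another type: 2 × 1/4 × 2/3 = 1/3. As shares of moves between types this is 30%, 30% and 40%.

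**3. Drift, no preference.** The gap shifts by 0.25 × (fall in N). From 30 to 24 this is 0.25 × 6 = 1.5, from -7.5 to -6. Falls of 10% and 30% (to 27 and 21) give shifts of 0.75 and 2.25. The smoking share is 25% throughout.

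**4. Drift with a true, constant bias.** Give the smoking image weight 1.5 and each other image 1, total 4.5. The shares are 33.3% smoking, 22.2% neutral and 44.4% high valence.
- Raw smoking minus neutral: 10 - 6.67 = 3.33 at N = 30, and 8 - 5.33 = 2.67 at N = 24.
- Smoking minus half the high-valence count: the same 3.33 and 2.67, so dividing by the number of images does not remove the drift.
- Smoking share minus neutral share: 11.1 percentage points at both totals.

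**5. Simulated rejection at two-sided 5%.** 1,000 runs, 25 per arm, 16 slides, two sessions; assumed SD of the total 4 between and 2 within subjects. These are t-tests on single contrasts, not the full ANOVA.

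| Contrast | Result |
|---|---|
| Image type, smoking vs high valence, raw, no preference | 100% |
| Image type, smoking vs neutral, no preference | 4% |
| Session change in smoking - high valence, no preference, N stays at 30 / falls to 29 / 27 / 24 | 4% / 16% / 82% / 100% |
| Session change in smoking - neutral, no preference, same four cases | 4-5% |
| Active vs sham change in smoking - high valence, both arms drift alike | 5-6% |
| Same, N falls 30 to 24 in one arm only | 83% |
| True constant bias 1.5, N falls 30 to 24: session change in raw smoking - neutral | 89% |
| Same: smoking - half of high valence | 96% |
| Same: smoking share of all fixations | 6% |

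**The case against.** Several counter-arguments stand and limit the point.

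- **Session change.** A reader might infer that a change in bias over sessions also arises by construction. It does not. The layout is the same at every session, so with stable totals it cancels (4% false session change). Drift is needed, and the protocol neither states nor excludes it.
- **Arm comparison.** A reader might infer that active versus sham is biased. That needs drift that differs by arm, for which the documents give no ground.
- **Scope.** Average fixation duration and average saccadic amplitude do not grow with the number of images, and the face slides are balanced. For the high-risk slides no image-type factor is named, so the layout matters there only if counts are compared by type.
- **Smoking versus neutral.** This is the common comparison that the protocol itself describes, and it is balanced 1:1. It is safe from the layout, but as a raw count it still moves with drift when a true bias exists, and the protocol expects such a bias in this population.
- **Hypotheses.** None of them says that smoking images draw more fixations than high-valence images. In the no-preference example the gap moves towards smoking, against hypothesis 3. But the smoking count alone falls from 7.5 to 6, and under a true bias smoking minus neutral falls too. The direction depends on which contrast is read.
- **Scoring rule.** That the counts are unnormalised is inferred from silence; the parameter list is not closed, and an unseen analysis plan may define the scoring. Against this, the protocol itself names the measures, the factor levels and the model.

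**Conclusion.** The concern holds in a limited form. For the numbers of fixations and transitions, as the protocol lists them, the smoking-versus-high-valence part of the image-type effect is built in: 25/25/50% of fixations without any preference, a gap of -5 to -8.75 per slide for assumed totals of 20 to 35. That term cannot be read as attentional bias.

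The image type by session term, and the within-subject session comparison used for hypothesis 3, are vulnerable rather than shown to be wrong. They change with no change in attention share if total fixations drift. A fall from 30 to 24 moves the gap by 1.5 fixations per slide. Both totals are assumptions, as are the spreads behind the simulated rates. The conclusion also assumes that counts are summed by type without normalisation. It concerns one secondary outcome family in a 50-person proof-of-concept trial, but hypothesis 3 has no arm without varenicline to absorb drift, so the scoring is worth correcting.

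**What to change.** In the eye-tracking part of Data Analysis, define the count-based scores relative to the slide:

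- Score fixations, and fixation time, on each image as a share of the slide total, and average the shares of the two high-valence images.
- Use smoking share minus neutral share on the same slide as the main smoking-bias score, and the corresponding high-risk minus neutral score on the high-risk slides.
- Express transitions per image and relative to total transitions. Count moves between the two high-valence images as well; if they are left out, halving the 40% above gives 20% per image against 30% for smoking, and the comparison is again uneven.
- Do not rely on dividing counts by the number of images alone. That removes the layout effect but not the drift when a true bias exists.

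Raw counts can stay as descriptive measures. The cost is rescoring gaze data that are recorded anyway; no slides, visits or participants are added. If the scoring software already works with shares, one sentence saying so is enough.

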**METHODS**

**Design**

This will be a double-blind sham-controlled two-arm randomized clinical trial. Fifty participants will be randomized (1:1) to each arm. Arm 1 will be active tDCS plus varenicline (n=25) and Arm 2 will be sham tDCS plus varenicline (n=25). Treatment duration will be 12 weeks. Subjects will be required to attend an in person assessment visit. They will then be randomized to a condition. Neuroimaging scans (fMRI) and eye-tracking tests will be conducted in all participants at baseline. Participants will undergo two scans at baseline on different days within the same week: one in a satiated state and one in a non-satiated state. The same tasks will be performed at each scan. s. Following the baseline fMRI scans and eye-tracking tests, subjects will start taking the varenicline simultaneous with starting the tDCS regimen whereby they will come to the clinic every day (Monday to Friday) for the first 2 weeks to undergo the stimulation (active: 20 minutes at 2mA, sham: 30 seconds at 2mA and then nothing). Their target quit date will be at the end of this 2 week period. They will return to the clinic every two weeks for the next 10 weeks for a booster tDCS session and to complete questionnaires. Eye tracking tests will be conducted at the end of the fourth and eighth weeks. At the end of the 12-week treatment period they will undergo a third fMRI scan and eye-tracking tests. For the next 14 weeks they will be contacted weekly by e-mail or text message to report on their smoking status as measured by the 7 day point prevalence abstinence question. “Have you had a cigarette, even a puff, in the last 7 days?” At the 6-month time point subjects will be asked to return to the clinic for a brief visit to confirm smoking abstinence using expired CO and urinary cotinine and to complete questionnaires.

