**Eye Tracking**

The eye tracking component to this study will attempt to answer several research questions. Specifically, does the magnitude of within-subject changes in VSB to smoking cues/and or emotional cues predict successful cessation and long-term abstinence? Does active tDCS change VSB to smoking cues, negative emotional cues or high-arousal/high-risk cues? Are within-subject changes in VSB to smoking/and or emotional cues correlate with the individual’s cravings? Does the individual’s VSB to high-arousal/high-risk cues correlate with long term treatment outcome? Eye movements will be recorded by Visual Attention Scanning Technology (VAST) (EL-MAR Inc. Toronto, Ontario Canada) (Guestrin and Eizenman, 2006, Pinhas et al., 2014, Chau et al., 2016) on five separate occasions (baseline, 4-weeks after start of treatment, 8-weeks after start of treatment,at the end of treatment -12-weeks and 6 months follow up). During each session, we will measure: 1) attentional bias to smoking cues, 2) attentional bias to negative emotional cues, and 3) attentional bias to high-arousal/high-risk cues.

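### The five-session repeated-measures ANOVA for eye-tracking is complete-case in its classical form, so a missed month-6 visit also discards on-treatment data from the active-versus-sham comparison

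*Protocol*

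**What the plan says.** Under Data Analysis (eye-tracking part), the protocol names the method twice. The fuller statement is "By means of a mixed design repeated-measures ANOVA, the VAST parameters will be compared within-subjects at 5 sessions". The factors are image type and session within subjects and arm between subjects: "session (sessions 1, 2, 3,4 and 5) and the between-groups factor is group (active tDCS and sham tDCS". The same paragraphs also say "The outcome measures of this paradigm will be analyzed using a mixed-model analysis of variance (ANOVA", and, on the arm comparison, "The parameters will also be compared between the two groups of subjects to examine the treatment effects of active tDCS". No model restricted to the on-treatment sessions is named.

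The Eye Tracking section fixes the timing: baseline, week 4, then "8-weeks after start of treatment,at the end of treatment -12-weeks and 6 months follow up". The Abstract gives the same five occasions. Session 5 therefore falls 14 weeks after week 12 (26 − 12 = 14).

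The Design section gives the arm sizes, "Arm 1 will be active tDCS plus varenicline (n=25) and Arm 2 will be sham tDCS plus varenicline (n=25", and limits contact between week 12 and month 6 to weekly e-mail or text. It then says "At the 6-month time point subjects will be asked to return to the clinic for a brief visit". That sentence lists CO, cotinine and questionnaires but not eye-tracking, so session 5 rests on the Abstract and the Eye Tracking section.

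On software: "All data analysis will be conducted using SPSS, SPM or R as appropriate". The Sample Size and Data Analysis sections name SPSS partial η2 as the effect-size measure for the treatment outcome.

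**The concern.** A classical mixed-design (split-plot) ANOVA needs each participant to have a value at every level of the within-subject factor. With session at five levels, a participant seen at baseline and weeks 4, 8 and 12 but not at month 6 leaves the whole model. That includes the week-12 comparison, for which the data exist.

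The on-treatment comparison of active with sham is thus made to depend on attendance at a visit long after stimulation and varenicline have ended. Two things are at stake. One is loss of valid data from a 50-person trial on a listed key secondary outcome and on hypothesis 4, which is the active-versus-sham contrast. The other is that the comparison would be among those who came back at month 6 rather than among all randomised participants. The second matters only if return depends on something linked to outcome. Smoking status is the obvious candidate, because the protocol's own hypotheses tie relapse to arm and to attentional bias.

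**Working it through.** **Inputs.** From the protocol: 25 per arm; five sessions, the last at month 6; a 40% sham abstinence rate (Sample Size section); two-tailed α of 0.05 and 80% power (Data Analysis). The protocol gives no sample-size or power figure for eye-tracking, so there is none to reproduce. Its only such statement concerns abstinence and is not used here. It gives no attendance rate, so every retention value below is an assumption.

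**Step 1: the mechanism.** In simulated data on ten people with five sessions each, one of the 50 observations was removed. A classical repeated-measures ANOVA routine (Python statsmodels) rejected the data as unbalanced, so that person would have to be dropped. A linear mixed model kept all ten people and 49 observations. SPSS itself was not run.

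**Step 2: cost in precision.** For a simple two-group contrast, the detectable standardized difference is d = (1.960 + 0.842) × √(2/n), with n per arm and losses spread evenly over the arms.

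| Analysed per arm | Share lost at month 6 only (assumed) | Detectable d | Power at d = 0.8 |
|---|---|---|---|
| 25 | 0% | 2.802 × √(2/25) = 0.79 | 81% |
| 20 | 20% | 2.802 × √(2/20) = 0.89 | 72% |
| 18 | 28% | 2.802 × √(2/18) = 0.93 | 67% |
| 15 | 40% | 2.802 × √(2/15) = 1.02 | 59% |

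At 20% loss the standard error grows by √(25/20) = 1.12, about 12%. The full ANOVA has more structure than this contrast, so the proportional loss is a better guide than the absolute values of d.

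**Step 3: scattered absences.** Suppose each post-baseline session is missed independently with probability m. Complete cases over five sessions number 50 × (1 − m)⁴; over sessions 1 to 4 they number 50 × (1 − m)³.
- m = 5%: 40.7 against 42.9.
- m = 10%: 32.8 against 36.5.

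Dropping month 6 from the model would therefore recover only part of the loss. If absences cluster in the same people, fewer are lost than these figures show.

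**Step 4: is the analysed sample enriched for quitters?** With quit rate q and return rates r_q (quitters) and r_n (non-quitters), the quitter share among completers is q·r_q / (q·r_q + (1 − q)·r_n). At q = 40%:
- 80% and 80% returning: 0.32/0.80 = 40%, no enrichment.
- 90% and 70%: 0.36/0.78 = 46%.
- 70% and 90%: 0.28/0.82 = 34%, the reverse.

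**Step 5: does that move the arm comparison?** Assume 60% quitters on active and 40% on sham, a gap of 20 points.
- 90% and 70% returning: active 0.54/0.82 = 65.9%, sham 0.36/0.78 = 46.2%, gap 19.7.
- 90% and 50% returning: active 0.54/0.74 = 73.0%, sham 0.36/0.66 = 54.5%, gap about 18.4.

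Both arms shift together. An illustrative simulation used the same quit rates, a direct arm effect of −0.3, a quitting effect of −0.8, unit residual SD, and return depending only on quit status. The true contrast is −0.3 − 0.8 × 0.2 = −0.46. The complete-case mean was −0.46 at 90%/70% and −0.44 at 90%/50% and at 95%/40%. The SD of the estimate rose from about 0.30 to 0.34–0.37.

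**The case against.** The protocol nowhere says that incomplete participants are excluded. It also uses the label mixed-model, allows R, and may leave missed sessions to a statistical analysis plan that is not shown. This stands in part: complete-case deletion belongs to the classical implementation and is not protocol text. But the mixed-model label is followed by the same within- and between-group factors, with no random effect, covariance structure or likelihood estimation mentioned. The reliance elsewhere on SPSS partial η2 points the same way, although that metric is attached to the treatment outcome. The classical reading is the natural one, and the method is named here, not left open.

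It can also be said that the five-session comparison is assigned to the effect of varenicline, with the arm comparison in a separate sentence. Yet the factor list puts session and group in one model, and no other model is given for the arm comparison.

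A reader might infer that the analysed sample is enriched for quitters and the arm contrast therefore biased. The documents do not support that as a fact. They give no retention by smoking status; enrichment vanishes under equal return and reverses if quitters return less. Weekly contact and a $50 payment for the month-6 visit favour retention. Even under differential return, the arm contrast hardly moved in the illustrations above.

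A reader might also carry the point over to the craving and CO analyses. The ANOVA described for them spans ten sessions and does not include month 6, so this argument does not reach them.

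Finally, this is a secondary outcome in a proof-of-concept pilot, and the primary abstinence outcome is untouched. That limits the weight of the point without removing it.

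**Conclusion.** The point holds in a limited form. Read naturally, the named five-session ANOVA is a complete-case analysis that ties the on-treatment comparison of active with sham to month-6 attendance and discards valid data.

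The firm cost is precision: with an assumed 20% missing month 6 only, 40 of 50 are analysed and the detectable difference rises from about 0.79 to 0.89. Over-representation of quitters is possible but conditional on non-quitters being lost more often, and any resulting bias in the arm contrast may be small. The conclusion rests on the classical implementation being used and on assumed attendance. It is worth correcting because a better method costs little, but it does not threaten the trial's main result.

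**What to change.** In Data Analysis, replace the eye-tracking ANOVA by a linear mixed model fitted by REML, using every available session of every randomised participant.

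- **Terms:** group, session, image type and their interactions; or group, session and group-by-session on a derived attentional-bias score. A model with neither image type nor such a score would not test attentional bias.
- **Baseline:** either keep it as a session or use it as a covariate for the post-baseline sessions, not both.
- **Contrasts:** report active versus sham at week 12 and at month 6 separately, so that the first no longer depends on attendance at the second.

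The cost is a change of wording: SPSS and R, already named, both fit the model, and no new data are needed. One small downside is that partial η2 does not come directly from this model, so a standardized contrast with its confidence interval should be reported for this secondary outcome. The model also relies on absence being explained by the observed data. It recovers the on-treatment data in full for those lost only at month 6, but it cannot guarantee an unbiased month-6 contrast.
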